### Primary outcome analysis

Referring to the CONSORT guidelines for non-inferiority trials [27], our analysis of non-inferiority will be limited to participants who adhere to the study protocol (per-protocol analysis). That means we will only include participants who have been randomly allocated, have complete data, and attended at least five out of seven iSMT or gSMT sessions. To declare non-inferiority, the upper bound of the 95% confidence interval (CI) for the difference in mean scores on the PSS between iSMT and gSMT must be below the margin ∆. For non-inferiority, we also will conduct a separate analysis based on an intention-to-treat (ITT) sample, including all randomly-allocated subjects, to test for iSMT superiority with a one-sided alpha error set at α = .05. This procedure has been found appropriate for non-inferiority evaluations [27, 70]. For analysis of the primary outcome, we will use linear models adjusted for the baseline outcome value and stratification variable. The primary outcome will be perceived stress at T3.

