As for any complex intervention, beyond comparative efficacy and cost-effectiveness, it is important to obtain insights into moderators of the SMT under study [35]. While assessing the non-inferiority of iSMT, in terms of reducing stress, it would also be valuable to explore if there are indicators that identify who benefits most from which SMT format. Research on moderators of either format, however, is scarce. For group stress management training, different intervention- and person-related moderators of efficacy have already been studied (e.g., intervention length, an intervention’s number of components, industry sector) [10] without generating clear conclusions for implementation in occupational settings. On average, iSMT yields greater effects when complemented with guidance through personal contact, contrary to pure self-help interventions [19, 20] and when it takes no more than nine weeks to finish the intervention [19]. Identifying moderators for each of these formats would provide novel information for intervention developers and decision makers, both in public and occupational health, especially if non-inferiority is established. For example, one study evaluating how well different health service formats were accepted by respondents of the general population revealed that people found face-to-face counselling and therapies more useful than Internet-based counselling, and that participants reported greater intentions to use face-to-face services to address emotional problems [36]. Similarly, respondents to another survey preferred traditional face-to-face stress management over Internet-based stress management [37]. To our knowledge, no study to date has empirically investigated the characteristics of the different training formats as potential moderators of these interventions’ efficacy.

In keeping with the above issues, the primary objective of this pragmatic trial is (1) to test the hypothesis that the iSMT intervention “GET.ON Stress” [29] is non-inferior to the gSMT intervention “Gelassen und sicher im Stress – calm and safe under stress” [32, 33] in employees, in terms of reducing perceived stress. Further aims are (2) to compare the two conditions from a cost perspective, and (3) to explore moderators of this comparative efficacy.

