### Statistical analysis

### Sample size

We used a multi-method approach to calculate the sample size required for this trial [69]. Sample size was calculated using a non-inferiority criterion, based on previous meta-analytic evidence for the reference group (gSMT). In a systematic meta-analysis, Richardson & Rothstein identified an effect of d = 0.73 on stress reduction for occupational stress management interventions, relative to being on a waiting list [10]. This effect would correspond to 4.6 points on the PSS, assuming a standard deviation of 6.3 points, derived from normative sample data from German employees [50]. In addition, we took anchor-based clinical judgement of a meaningful difference in primary outcome measure scores into account. We conducted two focus groups with clinical (*n* = 4) and occupational health experts (n = 4). All the focus group members agreed that a reduction of at least 3 points on the PSS would display a meaningful difference for people with elevated levels of stress at baseline (PSS score ≥ 22). Finally, we set the non-inferiority margin ∆ at 2 points on the PSS at T3. Based on the predefined margin, we need 314 subjects to reject the null hypothesis of inferiority of the iSMT with 80% statistical power, assuming deterioration of not more than 2 points relative to gSMT, with two-sided α = .05. Based upon previous studies on the Internet-based intervention [29, 30], we expect that approximately 30% of participants will drop out of the study during the intervention phase (between T1 and T3). Accordingly, we aim to recruit 448 participants.

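### Non-inferiority can be declared from the per-protocol, complete-data set alone; the ITT set is used only to test superiority

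*Protocol article*

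**What the plan says.** All of the relevant text is in the protocol article.

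- **Set for the decision** (Primary outcome analysis): "our analysis of non-inferiority will be limited to participants who adhere to the study protocol (per-protocol analysis". To qualify, a randomised participant must "have complete data, and attended at least five out of seven iSMT or gSMT sessions".
- **Decision rule** (same section): "To declare non-inferiority, the upper bound of the 95% confidence interval (CI" for the iSMT minus gSMT difference in mean PSS must be below the margin. Sample size fixes that margin: "we set the non-inferiority margin ∆ at 2 points on the PSS at T3".
- **Role of the ITT set** (same section): a "separate analysis based on an intention-to-treat (ITT) sample, including all randomly-allocated subjects, to test for iSMT superiority", at one-sided 0.05. The sentence opens with a reference to non-inferiority, but the only purpose it states is superiority.
- **Model** (same section): a linear model adjusted for baseline PSS and the stratification variable.
- **Purpose** (Background): the non-inferiority hypothesis is "the primary objective of this pragmatic trial", and the title calls the trial a comparative-effectiveness study.

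Nowhere is an ITT interval set against 2 points, and no rule covers disagreement between the two sets.

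**The concern.** Attending five sessions and providing complete data both happen after randomisation, and both can depend on the format received and on how the participant is doing. Once participants are selected on them, the arms need no longer be comparable, and adjusting for baseline PSS and stratum does not restore comparability.

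The document itself makes unequal selection plausible. One arm works through weekly online modules at its own pace. The other waits for groups to fill and then attends fixed workshops. About 30% dropout by T3 is expected even before the session rule removes anyone.

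Under the rule as written, non-inferiority could be declared although the ITT interval includes differences above 2 points, and the plan would not treat that as a conflict. The conclusion would apply to those who completed enough of their course, whereas a pragmatic question concerns everyone offered it.

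**Working it through.** **1. The plan's own figure.** Inputs from Sample size: margin 2, SD 6.3, two-sided alpha 0.05 (one-sided 0.025), power 80%. A true difference of 0 and 1:1 allocation are assumed; the allocation ratio is not stated.

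- Normal approximation: n per arm = 2 × (1.960 + 0.842)² × 6.3² / 2² = 155.8, so 156 per arm and 312 in total.
- The noncentral t version gives 157 per arm, 314 in total, as stated.
- Dropout: 314 / 0.70 = 448.6, stated as 448.

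The sample size reproduces.

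**2. The session rule by arm.** iSMT has seven weekly modules, so five separate modules are needed. Table 2 places the seven gSMT sessions on three training days, with 3, 2 and 2 sessions.

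| gSMT days attended | Sessions | Meets five of seven? |
|---|---|---|
| 1 and 2 | 3 + 2 = 5 | yes |
| 1 and 3 | 3 + 2 = 5 | yes |
| 2 and 3 | 2 + 2 = 4 | no |

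Two workshop days are enough in gSMT if day 1 is one of them. The same threshold therefore selects differently in the two arms.

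**3. Illustration of the effect on the error rate.** Suppose qualifiers score g points better than non-qualifiers in both arms, and fractions q(iSMT) and q(gSMT) are excluded. The per-protocol difference then moves towards iSMT by

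b = g × [q(iSMT) − q(gSMT)].

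With 157 per arm, SE = 6.3 × √(2/157) = 0.711. If iSMT is truly 2 points worse among all randomised, the chance of declaring non-inferiority is Φ(b/0.711 − 1.96).

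Neither g nor the retention split is in the document. Assume g = 3 and retention of 60% versus 80%, which averages the 70% that the protocol expects to stay in the study.

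| Retention iSMT / gSMT | b | Chance of false non-inferiority |
|---|---|---|
| 80% / 60% | 3 × (0.20 − 0.40) = −0.6 | Φ(−2.80) ≈ 0.25% |
| 70% / 70% | 0 | Φ(−1.96) = 2.5% |
| 60% / 80% | 3 × (0.40 − 0.20) = +0.6 | Φ(−1.12) ≈ 13% |

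Using the unequal arm sizes that 60% and 80% of 224 imply (134.4 and 179.2) gives SE = 0.719 and, for b = +0.6, 13.0%.

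**4. A second selection model.** Retention is taken to depend on a latent normal variable correlated with the outcome, with 60% (iSMT) and 80% (gSMT) of 224 per arm retained. Correlations of 0.1, 0.2 and 0.3 shift the difference towards iSMT by 0.19, 0.37 and 0.56 points, and the error becomes 4.4%, 7.4% and 11.8%. At 70% in both arms it stays at 2.5%.

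**5. Can the planned sample carry an ITT margin test?** At true difference 0 and SD 6.3, power is Φ(2/SE − 1.96).

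- All 448 fully informative: SE = 6.3 × √(2/224) = 0.595, power 91.9%.
- Only about 314 informative: SE = 0.711, power 80.3%.

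The actual value lies between these, depending on how much information is recovered for missing T3 scores.

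**The case against.** **Per-protocol analysis has a real role here.** Non-adherence can pull the arms together in an ITT comparison and so favour non-inferiority. This trial adds another reason for caution about ITT: T3 is fixed at three months after allocation, while gSMT participants wait for a group and are expected to start considerably later. Some may have had little training by T3, which could favour iSMT in the ITT set. This stands. It means that neither set is safely conservative, which argues for requiring both and does not justify relying on per-protocol alone.

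**The direction of bias is unknown.** The 30% dropout figure comes from studies of the Internet programme, and no retention figure is given for gSMT. Travel-dependent workshops after a wait could lose more people than the online course, and per-protocol would then be the stricter test. This also stands, and it is why the range above runs in both directions. Part of any gap between attenders and non-attenders may also be the genuine effect of training; to that extent the per-protocol set answers a different question and is not simply wrong.

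**The ITT sentence is ambiguous.** Its opening words could suggest an ITT analysis that supports the non-inferiority finding. An ITT model of T3 PSS is indeed planned, so a reader might wrongly infer that ITT is absent. What is missing is any use of it against the margin.

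**The cited guidance.** The section says that its procedure has been found appropriate and cites sources. These cannot be checked here and count for neither side.

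**Missing data.** The method for missing T3 scores is commonly left to the statistical analysis plan, so its absence is not part of this point.

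**Conclusion.** The point holds as a fault in the decision rule. The text positively restricts the non-inferiority decision to a set selected on post-randomisation adherence and data completeness, and gives the ITT set no part in that decision. This is a stated choice that governs the headline claim, not a detail lost when the article was condensed.

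The size is illustrative only. With SD 6.3, 157 per arm, a true 2-point deficit, an assumed 3-point gap and an assumed 20-point difference in retention, the false non-inferiority rate lies between about 0.25% and 13%, depending on which arm loses more. It is 2.5% when retention and selection are equal.

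Two stronger readings are tempting and unsupported. One is that the rule is biased towards iSMT: nothing in the document shows which arm will lose more participants, or which ones. The other is that the comparison is non-randomised in the sense of an observational study: it is a selected subset of a randomised trial, with adjustment for baseline PSS and stratum. The selection problem is real, but that label overstates it.

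**What to change.** Replace the decision rule in Primary outcome analysis with one along these lines: non-inferiority is declared only if the upper bound of the two-sided 95% CI for the iSMT minus gSMT difference in PSS at T3 is below 2 points in both the ITT set and the per-protocol set, and both results are reported side by side.

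The ITT set should include everyone randomised. Missing T3 scores can be handled by a likelihood or multiple-imputation model that uses the PSS scores Table 3 already schedules at the other assessments.

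Reword the sentence that introduces the ITT analysis so that the ITT margin test and the ITT superiority test are two separate statements.

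The cost is a few sentences and one further model comparison. Joint power will be slightly below the per-protocol power alone, because both intervals must clear the margin. No extra participants are needed: the planned sample gives the ITT margin test between about 80% and 92% power.

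### The ITT superiority test runs at one-sided α = .05, a looser level than the two-sided .05 used for the sample size and for non-inferiority on the same endpoint

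*Protocol article*

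**What the plan says.** Three statements in the protocol article set the level of evidence for PSS at T3.

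- **Sample size section:** "we need 314 subjects to reject the null hypothesis of inferiority of the iSMT with 80% statistical power", and the calculation is made "with two-sided α = .05". The margin is 2 points and the SD 6.3.
- **Primary outcome analysis section, non-inferiority:** in the per-protocol set, the criterion concerns "the upper bound of the 95% confidence interval (CI) for the difference in mean scores on the PSS between iSMT and gSMT", which has to lie under 2 points.
- **Primary outcome analysis section, superiority:** a separate analysis of all randomised participants is planned "to test for iSMT superiority with a one-sided alpha error set at α = .05".

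The section cites two sources for the procedure as a whole. It gives no specific reason why superiority is tested at a different level.

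**The concern.** A 5% two-sided level puts 2.5% in the tail that favours iSMT, whereas the superiority test puts 5% there. The same endpoint, and errors in the same direction, are thus held to two standards, and the looser one serves the claim that iSMT is better than the established group training.

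The article treats superiority as a possible result: its Study limitations section discusses what would follow from it. Its Discussion also warns that earlier comparisons may have leaned towards the digital format by design. At stake is a superiority statement that would fail the trial's own two-sided 5% criterion, and that readers would question as soon as they saw a conventional 95% interval beside it.

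**Working it through.** **Inputs.** From the Sample size section: margin 2, SD 6.3, power 80%, two-sided α = .05, 314 evaluable, 30% dropout, recruitment target 448. Assumed, because the article gives no figure: true difference 0 for the non-inferiority calculation, and 1:1 allocation.

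**Step 1: which level gives 314?** The normal approximation is n per arm = 2 × (z₁₋α + z₀.₈₀)² × SD² / margin².

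| One-sided α | Calculation | n per arm (normal) | Total (normal) | Total (noncentral t) |
|---|---|---|---|---|
| .025 | 2 × (1.960 + 0.842)² × 39.69 / 4 | 156 | 312 | 2 × 157 = 314 |
| .05 | 2 × (1.645 + 0.842)² × 39.69 / 4 | 123 | 246 | 2 × 124 = 248 |

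The plan's figure is reproduced exactly at one-sided .025 and not at .05. This settles a point that the non-inferiority sentence leaves open: its 95% CI is two-sided. Had it been a one-sided 95% bound, both tests would run at 5% and there would be no mismatch. Dropout: 314 / 0.7 = 448.6, consistent with the stated 448.

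**Step 2: the superiority threshold.** One-sided α = .05 rejects at z > 1.645. A two-sided 95% interval excludes zero on the favourable side only at z > 1.960. Results between the two are called superior although that interval includes zero. At zero true difference the test declares superiority with probability .05. In .05 − .025 = .025 of all trials, half of those false declarations, the two-sided 95% interval would include zero.

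**Step 3: the band in PSS points.** SE = 6.3 × √(4/N), without baseline adjustment. The last column is the two-sided 95% interval (iSMT minus gSMT) when the result lies exactly on the 1.645 boundary.

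| N analysed | SE | 1.645 × SE | 1.960 × SE | 95% CI at the boundary |
|---|---|---|---|---|
| 314 | 0.711 | 1.17 | 1.39 | −2.56 to +0.22 |
| 448 | 0.595 | 0.98 | 1.17 | −2.15 to +0.19 |

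The ITT set is all randomised participants, so 448 is the nominal number. With 30% expected dropout the effective information may lie between the two rows. The planned model adjusts for baseline PSS, which would reduce the SE and lower every point value. The z band from 1.645 to 1.960 does not depend on the SE.

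**Step 4: power given up by tightening.** Power = Φ(true advantage / SE − z₁₋α).

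| True advantage of iSMT | N | One-sided .05 | One-sided .025 |
|---|---|---|---|
| 1.0 | 314 | 41% | 29% |
| 1.0 | 448 | 51% | 39% |
| 1.5 | 314 | 68% | 56% |
| 1.5 | 448 | 81% | 71% |
| 2.0 | 314 | 88% | 80% |
| 2.0 | 448 | 96% | 92% |

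**The case against.** The level and its direction are stated in advance, and the test has exactly the 5% error it announces. A one-sided 5% test agrees with a 90% two-sided interval, and the article does not promise a 95% interval for the ITT analysis. The primary objective, the sample size and the main conclusions rest on non-inferiority, so superiority is supplementary. The sources cited for the procedure are not available here, so whether they cover this level cannot be checked.

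Most of this stands, and it limits the point. Prespecification does rule out a choice made after seeing the data. It does not explain why the same endpoint is held to two-sided 5% in one place and one-sided 5% in another.

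A reader might infer three stronger things that the article does not support:

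- **That one reported interval will contradict itself**, its upper bound being compared first with 2 and then with 0. No such interval is planned: non-inferiority uses the per-protocol set and superiority the ITT set. The discrepancy is between the ITT verdict and the two-sided 95% interval that would accompany the ITT estimate if it were reported.
- **That superiority is formally tested only after non-inferiority is shown.** The section calls it a separate analysis and states no clear order. The mismatch in level is the same either way.
- **That 1.17 to 1.39 points is a property of the planned test.** It holds only for 314 analysed with the unadjusted SD.

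**Conclusion.** The point holds as an inconsistency of level. The ITT superiority test carries a 5% false-superiority rate at zero true difference, against the 2.5% implied by the trial's own two-sided 5% level. It allows a superiority claim for any z between 1.645 and 1.960, where the two-sided 95% ITT interval would include zero. These statements need no assumption about the SD or the number analysed.

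The point values do: with 1:1 allocation and an unadjusted SD of 6.3, the band runs from about 1.17 to 1.39 with 314 analysed and from 0.98 to 1.17 with 448. Both would be lower after baseline adjustment.

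It would be wrong to conclude that the trial's primary error rate is inflated. The non-inferiority error rate and the sample size are untouched. The change is worth making because the present text lets a supplementary claim pass on weaker evidence than the trial requires for its main one.

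**What to change.** In the Primary outcome analysis section, set the ITT superiority test at one-sided α = .025. State the decision rule as an interval: superiority of iSMT is declared only if the upper bound of the two-sided 95% CI for the ITT difference in PSS at T3 (iSMT minus gSMT) is below 0. The wording should make clear that this interval comes from the ITT analysis and is distinct from the per-protocol interval used for non-inferiority.

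The edit changes one number and adds one clause. It alters neither recruitment, assessments nor the non-inferiority analysis. The cost is lower power for superiority, which the trial was not sized to show: under the assumptions above, the loss at a true advantage of 1.5 points is about 12 percentage points with 314 analysed and 10 with 448.

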## Methods

### Study design

The declaration of Helsinki for Ethical Principles for Medical Research Involving Human states that “The benefits, risks, burdens and effectiveness of a new intervention must be tested against those of the best proven intervention(s)” [38]. Accordingly, we will test the non-inferiority and cost-effectiveness of the relatively new iSMT intervention “GET.ON Stress” [29] against the best proven and probably most adopted intervention for stress management in Germany speaking countries, that is the gSMT intervention “Gelassen und sicher im Stress – calm and safe under stress” [32, 33]. In a randomized controlled trial, one group of participants will receive access to iSMT, whereas another group will participate in gSMT.”

Outcome assessments will take place at baseline (T1), and both three months (T3) and six months (T4) after allocation to the study conditions. To mimic real-life occupational practice, participants in iSMT will be granted access to the intervention immediately after randomization, whereas participants in gSMT will have to wait until a sufficiently large number of participants has been recruited and randomized into this condition to fill group sessions. For this reason, participants in each condition will also need to attend in a short extra assessment (T2) right before their first training session.

The primary outcome will be the level of perceived stress at T3. There will be no restrictions to the use of other care as usual (CAU). This study protocol describes the design of the pragmatic trial based on Standard Protocol Items: Recommendations for Interventional Trials (SPIRIT) guidelines [39]. The study also will be conducted in accordance with the Consolidated Standards of Reporting Non-inferiority Trials (CONSORT) [27].

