### Recruitment and procedures

Recruitment will occur in the winter through summer of 2022, employing two major strategies. To attract interested organizations, we will use different media channels to motivate owners of small- and medium-sized companies (staff headcount < 250) in the target region to offer the intervention to their workforce. To attract individuals, health insurance companies will advertise the study via announcements in print membership magazines and media channels (e.g., Facebook, Twitter). Registration into the study will take place at an individual level, so employees need not self-disclose to their employer that they want to participate. An open-access website will provide information on study conditions. Applicants will sign up by providing an email address and name or pseudonym on the website. Applicants who fulfill all inclusion criteria assessed by an online screening questionnaire, return their informed consent, and complete the baseline assessment (T1) will receive a phone call by a research assistant to inform them about further requirements for inclusion (e.g., time scheduling for each of the interventions) and to answer the applicants’ questions. Thereafter, each applicant will be randomly allocated to one of the study conditions (Fig. 1), with randomization stratified by whether or not employees work in companies concurrently conducting organizational mental health programs. Allocation concealment will be ensured by an independent researcher not otherwise involved in this study, who will randomize study participants with a separate randomization sequence for each strata (concurrent organizational health program = yes/no). We will use a restricted randomization procedure using varying block sizes of 4 to 6 generated by the software RandList (randomization.eu). This researcher will send randomization results to the study administration responsible for subject allocation. For practical reasons, blinding of participants will not be possible.

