After they are informed about the outcome of randomization, participants offered iSMT will receive immediate access to the program. Participants allocated to gSMT will receive information about the times and locations of group sessions; they then will need to select in which workshop they want to participate. Just before their first training session, all participants will need to complete a short pre-intervention assessment (T2). Participants will receive up to three automated e-mail reminders if they did not attend the assessments. All assessment and Internet-based training data will be collected using a secure assessment and training system (AES, 256-bit encrypted). Both the web-based assessment system and training platform are physically located on servers belonging to Leuphana University of Lueneburg. The principal investigator DL and the first author LB will have full access to the final dataset. Two researchers will assure data integrity, independently.

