### Outcome measures

#### Primary outcome

The primary outcome will be the level of self-rated stress (Table 3), measured using the Perceived Stress Scale (PSS-10) [49], a validated measure of stress that has been used extensively during evaluations of both in-person and Internet-based stress-management interventions. The PSS-10 assesses the extent to which participants experience their lives as stressful (e.g., as overstraining, unmanageable, and/or unforeseeable over the past month). It consists of ten items, each having the following 5-point Likert scale response options of 0 = never; 1 = almost never; 2 = sometimes; 3 = fairly often; and 4 = very often (summation score range 0–40). In this trial, respondents will answer items referring only to the past week. The German version of the scale has been validated in the general population [50]. An online version of the German scale has also been validated in samples of German employees, exhibiting good reliability with McDonald’s omega (ω) = .89 and good measurement invariance [51].

**Table 3 Tab3:** Outcome measures and assessment points

Outcome measures	T0	T1	T2	T3	T4
Perceived Stress Scale (PSS)	✓	✓	✓	✓	✓
Center for Epidemiological Studies on Depression Scale (CES-D)	-	✓	-	✓	-
Brief Resilience Scale (BRS)	-	✓	-	✓	-
Perceived Occupational Stress (POS)	-	✓	-	✓	-
Technology Readiness (TRI 2.0)	-	✓	-	-	-
Patient Questionnaire on Therapy Expectation and Evaluation (PATHEV) – adapted for stress management training	-	✓	-	-	-
Effort-Reward-Imbalance Questionnaire (ERI)	-	✓	-	✓	-
Job Crafting Scale (JCS) - adapted	-	✓	-	✓	-
Treatment Inventory of Costs in Psychiatric Patients (TIC-P), subscale for productivity loss	-	✓	-	-	✓
Health and Labor Questionnaire (HLQ)	-	✓	-	-	✓
Assessment of Quality of Life (AQoL-6D)	-	✓	-	-	✓
Client Satisfaction Questionnaire (CSQ/CSQ-I)	-	-	-	✓	-
Preferences for online and group stress management - self-developed	-	✓	-	✓	-
Adherence to the intervention - self-developed	-	-	-	✓	-
Beck Depression Inventory (BDI), suicide ideation item	✓	-	-	-	-
Socio-economic variables (staff headcount, including income from paid employment, history of health service use, current health-related change programs in the organization, preference for Internet-based vs. in-person group training for stress reduction)	✓	-	-	-	-

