Note: T0 = Screening for eligibility; T1 = Baseline Assessment; T2 = Pre-Intervention Assessment prior to intervention beginning; T3 = Post-Intervention-Assessment, 3 months after group allocation; T4 = Post-Intervention-Assessment, 6 months after group allocation

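### The primary model adjusts for one pre-randomisation PSS score (T1) although a second (T0) is also collected; adding T0 is an optional, small precision gain, not the repair of an error

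*Protocol article*

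**What the plan says.** Under Primary outcome analysis, the protocol article specifies "linear models adjusted for the baseline outcome value and stratification variable" for PSS at T3. The wording is singular: one baseline value of the outcome. Study design shows which one is meant: "Outcome assessments will take place at baseline (T1), and both three months (T3) and six months (T4) after allocation". The note to Table 3 separates the two early time points: "T0 = Screening for eligibility; T1 = Baseline Assessment".

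Table 3 ticks the PSS at all five time points, T0 to T4. Recruitment and procedures gives the order of events. "Applicants who fulfill all inclusion criteria assessed by an online screening questionnaire", who also return consent and complete T1, receive a phone call. Then comes allocation: "Thereafter, each applicant will be randomly allocated to one of the study conditions". T0 and T1 therefore both precede randomisation, while T2, taken just before the first session, follows it.

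The eligibility criteria under Participants contain no PSS threshold. The reliable-change analysis runs from T1 to T3. The article states no use for the T0 PSS, either as an entry criterion or as a covariate.

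**The concern.** Non-inferiority is declared if the upper 95% confidence bound for the difference in mean PSS lies below 2 points. The width of that interval depends on the residual variance after covariate adjustment. The PSS in this trial refers to the past week only, so a single score mixes a person's usual level with that week's fluctuation. A second score on the same scale, also taken before randomisation, may carry further information about T3.

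Because no PSS cut-off governs entry, T0 is not truncated by selection, and adjusting for it cannot bias the treatment comparison. What is at stake is a modest amount of precision that the trial could have from data it already plans to collect.

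**Working it through.** **Inputs from the article (Sample size; Primary outcome analysis).** Margin 2 points, SD 6.3, two-sided alpha 0.05 (one-sided 0.025 for the bound), power 80%, 314 evaluable. Equal allocation and a true difference of zero are assumed, because neither is stated.

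**Reproducing the stated figure.** Normal approximation: n per arm = 2 × (1.96 + 0.8416)² × 6.3² / 2² = 155.8, so 156 per arm and 312 in total. With the noncentral t distribution it is 157 per arm, 314 in total, with power 80.1%. The 314 reproduces. It uses the unadjusted SD, so it takes no credit for any covariate, not even T1.

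**Adding covariates.** Let a = corr(T1, T3), b = corr(T0, T3) and c = corr(T0, T1). None is in the article, so all three are assumptions.

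- T1 only: residual variance factor = 1 − a².
- T0 and T1: factor = 1 − (a² + b² − 2abc) / (1 − c²).

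With a = 0.5, T1 alone gives 0.750. The SD becomes 6.3 × √0.750 = 5.46, and power at 157 per arm is 89.9%. The 95% half-width is 1.96 × 5.46 × √(2/157) = 1.21 points.

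Worked case, b = 0.45 and c = 0.8: (0.25 + 0.2025 − 0.36) / 0.36 = 0.2569. The factor is 0.743, and the further fall is 1 − 0.743/0.750 = 0.9%.

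Equivalent extra participants are 314 × 0.750 / factor − 314.

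| c (T0-T1) | b (T0-T3) | Factor | Further fall | Equivalent participants | Power |
|---|---|---|---|---|---|
| 0.7 | 0.50 | 0.706 | 5.9% | 20 | 91.6% |
| 0.7 | 0.45 | 0.730 | 2.6% | 8 | 90.7% |
| 0.7 | 0.40 | 0.745 | 0.7% | 2 | 90.1% |
| 0.8 | 0.50 | 0.722 | 3.7% | 12 | 91.0% |
| 0.8 | 0.45 | 0.743 | 0.9% | 3 | 90.2% |
| 0.8 | 0.40 | 0.750 | 0% | 0 | 89.9% |

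The gain is exactly zero when b = a × c, that is, when T0 predicts T3 only through T1. Here 0.5 × 0.8 = 0.40, the last row. In the most favourable row the half-width goes from 1.21 to 1.17 points, a standard error about 3% smaller (√(0.706/0.750) = 0.970).

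**The case against.** The strongest reply is that nothing here is wrong. Analysis of covariance on one baseline value plus the stratification factor is a standard primary model. It is unbiased, and type I error, margin and decision rule are unaffected. The sample size takes no credit for covariates, so T1 adjustment alone already puts power above the planned 80% if T1 and T3 are correlated at all. All of this stands.

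The reply continues that the benefit may be nil. T0 lies further from T3 than T1 does, so its correlation with T3 may well be lower, and a shortfall of 0.05 to 0.10 removes most or all of the gain. If screening and baseline are close together, their past-week windows overlap and T0 adds little. This also stands, and it is why the range starts at zero.

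Finally, that every randomised participant has a T0 score is an inference from Table 3 and the mandatory screening step. Study design does not list T0 among the assessments, and the screening questionnaire is described as assessing inclusion criteria, of which PSS is not one. The inference is reasonable but should be confirmed.

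Two stronger readings are tempting. A reader might infer that leaving out T0 makes the trial underpowered or its primary analysis faulty; the reproduced 314 and the validity of the T1-only model rule that out. A reader might also infer a large gain. Setting all three correlations to 0.6 gives factors of 0.640 and 0.550, a 14% fall worth about 51 participants. But that requires screening stress to be no more closely related to baseline stress than to stress measured three months after allocation. Nothing in the article supports that case.

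**Conclusion.** The point holds as a minor, optional improvement. The article schedules two pre-randomisation scores on the primary outcome scale and gives the primary model only one of them. The stated model, sample size and power are sound as they are.

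Under the correlations tabulated, the benefit runs from nothing to about a 6% further fall in residual variance, with power at most about 1.7 percentage points higher. These figures rest on assumed correlations, equal allocation, SD 6.3, 314 evaluable participants and no true difference.

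The case for acting is that the potential gain is nearly free and carries no risk of bias, provided the choice is made before outcome data are seen. Adding the covariate later would invite the suspicion that the model was chosen for its result.

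**What to change.** In Primary outcome analysis, replace the single baseline value with PSS at T0 and PSS at T1, alongside the stratification variable, in both the per-protocol and the intention-to-treat models. Pre-specify this and confirm that T0 PSS is recorded for everyone randomised. Alternatively, state why T0 is not used.

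Entering the two scores separately is safer than entering their mean, although the mean is an acceptable simpler form. The mean forces equal weights: with a = 0.5, b = 0.40 and c = 0.8, its squared correlation with T3 is (a + b)² / [2(1 + c)] = 0.81 / 3.6 = 0.225. That leaves a factor of 0.775, worse than 0.750 with T1 alone.

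T2 should stay out of the model. It follows randomisation, and the wait before the first session differs between arms by design.

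The cost is one sentence in the plan and one degree of freedom. No further data collection is needed, and the sample size need not change.
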